### Treatment adherence

Global PA practices, specific exercises and use of the education booklet will be reported in a self-reported questionnaire at 3 months to assess level of adherence to the self-management exercise program [26]. Reasons for low adherence will be explored: therapeutic effect, novelty, social link, global health, body image, habits.

### Time-point outcomes

Study outcomes will be collected at baseline and after treatment (18 days) in spa resorts and at 3 months post-randomisation, by mailed self-reporting questionnaires. If needed, the research officer will use a telephone follow-up.

### Statistical considerations

#### Sample size estimation

According to previous works presented in literature [11], we have estimated that a sample size of *n* = 65 patients per randomized group, for a two-sided type I error at 5%, would provide 80% statistical power of detecting an absolute difference of 20% (25% vs 5.) in the primary outcome: proportion of participants varying to one IPAQ class at least (low-moderate or high or moderate-high). Finally, a total of *n* = 142 patients (71 by group) will be considered to take into account lost to follow-up (10%).

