**Methods:**

We aim to perform a prospective, multicentric, quasi-randomized controlled trial with an alternate-month design (1-month periods). People aged 50–75 years old with symptomatic knee OA (stage I-IV Kellgren and Lawrence scale) with low and moderate PA level will be included in 3 spa therapy resorts. The experimental arm will receive 5 self-management exercise sessions (1.5 h each; education, aerobics, strength training, range of motion) + an information booklet + 18 sessions (1 h each) of spa therapy treatment (STT). The active comparator arm will receive an information booklet + 18 sessions of STT. The primary outcome will be a change at 3 months in PA level (International Physical Activity Questionnaire short form score). Secondary outcomes will be function (WOMAC) pain (numerical scale), anxiety/depression (HAD), fears and beliefs about OA (KOFBeQ) and arthritis self-efficacy (ASES). The barriers to and facilitators of regular PA practice will be assessed by using specific items specifically designed for the study because of lack of any reference scale.

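### The stated 80% power does not match the stated inputs: for 25% vs 5%, 65 per group gives about 90% under independence, and 80% needs only 49

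*Protocol article*

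**What the plan says.** The section Sample size estimation gives a complete set of inputs: "65 patients per randomized group", "for a two-sided type I error at 5" per cent, and "an absolute difference of 20% (25% vs 5" per cent. (The percent sign after the 5 is missing in the text, but the 20-point difference fixes the value.) It says that this size "would provide 80% statistical power of detecting an absolute difference of 20" percentage points in the primary outcome, the proportion moving up at least one IPAQ class by 3 months. The total is then raised to "142 patients (71 by group") "to take into account lost to follow-up (10" per cent).

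The section Statistical analysis tests this outcome with a chi-squared or Fisher's exact test on individual patients. A supporting mixed model has centre as its random effect. The Abstract describes a "quasi-randomized controlled trial with an alternate-month design (1-month periods"), and the section Randomisation says that groups of patients are assigned to arms, stratified by centre. The sample size section mentions no design effect, intracluster correlation (ICC) or number of periods.

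**The concern.** Power, rates, significance level and sample size are tied together: any three fix the fourth. Here all four are stated and they conflict. This is the trial's only justification of its size. A reader who repeats the calculation gets 49 per group. That reader cannot tell whether the other 16 reflect a 90% target, a misprinted rate, an unstated margin or a slip.

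The conflict matters a little more because of the design. The calculation is one for independent patients, while allocation is by month within centre. Without the correct power under independence, nobody can judge how much correlation within months the trial could absorb.

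**Working it through.** **Inputs** (all from Sample size estimation): p1 = 0.25, p2 = 0.05, difference 0.20, mean 0.15, two-sided α = 0.05 (z = 1.96), n = 65 per group, stated power 80%, enrolled 71 per group, loss 10%.

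**Step 1: trying to reproduce 65 at 80% power.** Pooled formula:

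n = [1.96·√(2·0.15·0.85) + z_β·√(0.25·0.75 + 0.05·0.95)]² / 0.20²

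The two root terms are √0.255 = 0.505 and √0.235 = 0.485.

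- 80% (z_β = 0.842): (0.990 + 0.408)² / 0.04 = 48.8, so 49 per group.
- 90% (z_β = 1.282): (0.990 + 0.621)² / 0.04 = 64.9, so 65 per group.

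Other versions for 80% power, per group: continuity-corrected 59 (58.4), unpooled 47, arcsine 45, one-sided 39 (48 with continuity correction). None gives 65.

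**Step 2: power at 65 per group.**

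| Method | Power |
|---|---|
| Pooled normal approximation | 90.1% |
| Chi-squared, exact enumeration | 92.1% |
| Fisher's exact, exact enumeration | 88% |
| Continuity-corrected formula | 84.8% |

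The stated 80% is outside this range.

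**Step 3: loss to follow-up.** 71 × 0.9 = 63.9, so about 64 evaluable per group. To keep 65 after 10% loss, 65/0.9 = 72.2, so 73 per group (146 in total). Put the other way, 71 per group can lose 6 patients, and 6/71 = 8.5%. At 64 per group the pooled power is 89.6%.

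**Step 4: room for correlation within months.** On the pooled formula, 65 per group keeps 80% power up to a design effect of 65/48.8 = 1.33. With 63.9 evaluable this is 63.9/48.8 = 1.31. Against the continuity-corrected requirement it is smaller: 65/58.4 = 1.11.

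The documents give neither an ICC nor the number of patients per centre-month, so the following is purely illustrative. The design effect is 1 + (m − 1)·ICC, with 65 per group and the pooled formula.

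| Patients per centre-month (assumed) | ICC 0.05 (assumed) | ICC 0.10 (assumed) |
|---|---|---|
| 2 | 88.6% | 87.1% |
| 3 | 87.1% | 84.0% |
| 6 | 82.5% | 75.0% |
| 12 | 73.6% | 60.0% |

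An m of about 2 follows if 142 patients were spread evenly over 3 centres and all 24 months of the 2-year trial (142/72 = 1.97), which is itself an assumption.

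**The case against.** Four objections deserve an answer.

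**The error is on the safe side.** Under the trial's own assumptions it has more power than it claims, and no decision on size changes. This stands, and it limits the seriousness of the point.

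**The power label may not be the wrong item.** The rates rest on a cited source that is not available here, and the text is damaged at that spot. With the same 20-point difference but 30% vs 10%, 65 per group would give 82%. So the figures prove a conflict, not which of them is wrong. The exact match of 65 to the 90% requirement makes a misstated power the likelier explanation, but the sponsor has to confirm it.

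**A reader might infer that allocation by month leaves the trial underpowered.** The documents do not support this. They give no ICC, and the only group size, 5 to 7, is that of an exercise session in the experimental arm, not recruitment per centre-month. Small clusters leave power comfortably above 80%; large ones do not. What stands is that no allowance is stated.

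**A reader might instead take the step from 49 to 65 as a deliberate margin for clustering.** The protocol never says so, and the exact match to the unclustered 90% figure argues against it.

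**Conclusion.** The stated power is wrong as written, if the rates are as printed. For 25% vs 5% at two-sided 5%, 65 per group gives about 90% (85% to 92% by method), and 80% needs 49 per group, or 59 with continuity correction. All of this assumes independent patients.

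The calculation carries no stated allowance for allocation by month within centre. On the pooled formula, power stays at or above 80% only while the design effect is at most about 1.33. Where the true design effect lies cannot be determined from the documents.

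The shortfall in the allowance for loss is real but trivial: one patient per group, and about half a percentage point of power. It may be tempting to conclude that 65 was simply multiplied by 1.1, but that gives 71.5, which rounds up to 72 rather than the stated 71, so the method used is unknown.

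This is a reporting error in a key paragraph. It should be corrected because it is the only basis given for the trial's size, but it is conservative under independence and does not call the sample of 142 into question by itself.

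**What to change.** Keep 142 patients and revise the sample size paragraph as follows.

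1. Check power, rates and sample size against the source calculation and correct whichever is misstated.
2. If 25% vs 5% is as intended, state that 65 evaluable patients per group give about 90% power assuming independent patients, and that 49 per group would suffice for 80%.
3. State that this figure makes no allowance for allocation by month within centre, and that on the pooled formula power stays at or above 80% only up to a design effect of about 1.33. Label any ICC or cluster size shown as an illustrative assumption. Do not describe the difference between 49 and 65 as a planned allowance for clustering.
4. Either state about 64 evaluable patients per group after 10% loss (still about 90% power under independence), or say that 142 patients tolerate about 8.5% loss if 65 per group are to remain.

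The cost is one reworded paragraph and a look at the original calculation. No extra patients are needed and no test changes.

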#### Statistical analysis

Statistical analyses will be conducted using SAS software (version 9.3.). A two-sided *p*-value of less than 0.05 will be considered to indicate statistical significance (except interim analysis).

Concerning the primary outcome, the comparison between groups will be analysed using Chi-squared or Fisher’s exact tests. Intention to treat (ITT) analysis will be considered for the primary outcome. Then, the analysis of the primary outcome will be completed by multivariate analysis using a generalized linear mixed model (logistic for dichotomous dependent endpoint) to take into account: (1) fixed effects covariates determined according to univariate results and to clinical relevance (for example gender, age and analgesic treatments), and (2) centre as random-effects (to measure between and within centre variability). Continuous endpoints will be compared between groups using Student’s t-test or Mann-Whitney’s test. Normality will be studied by the Shapiro-Wilk test and homoscedasticity using the Fisher-Snedecor test. As suggested by Vickers and Altman [40], the comparison between groups will be completed by linear mixed model considering randomization group and baseline values as independent parameters (fixed effects). Other categorical parameters will be analysed as described previously. Longitudinal analyses concerning repeated measures (for example ASES, KOFBeQ, WOMAC, EVA pain, fears and beliefs, assessed at baseline, after intervention and 3 months after intervention) will be studied using random-effect models (linear or generalized linear), to take into account patient as random-effect (slope and intercept), nestled in centre random-effect, while studying the fixed effects group, time and group *interaction x time*.

According to clinical relevance, sub-group analyses depending gender will be proposed after the study of sub-group x randomization group interaction in regression models (for repeated data or not). Secondarily, a per-protocol analysis will be considered. Finally, a sensitivity analysis will be performed and the nature of missing data will be studied (missing at random or not). According to this, the most appropriate approach to the imputation of missing data will be proposed (maximum bias (e.g. last observation carried forward vs. baseline observation carried forward) or estimation proposed by Verbeke and Molenberghs for repeated data). More precisely, concerning the IPAQ score, when participant will mention a number of days, hours or minutes for an activity without checking « yes » or « no » to intense, moderate or walking categories practice, a « yes » response will be imputed to this question. If participant no mentions to the practice of an activity or the number of days, hours or minutes, a « no » response will be imputed to this question.

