### Study design and setting

This is a 2-year multicenter, prospective, comparative, and quasi-randomized trial. The population will be randomised according to the alternate-month design method in 2 arms: experimental and active comparator.

The design and conduct of this trial will adhere to the requirements of the Standard Protocol Items: Recommendations for Interventional Trials (SPIRIT) [25]**.** The results will be reported in accordance with the CONSORT Statement for non-pharmacologic trials [26].

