### Participants and recruitment

We will recruit 142 participants, male and female, who are 50–75 years old with a diagnosis of mono or bilateral knee OA, in 3 spa therapy resorts, in France. All people already registered for STT will receive an information letter with study notification and eligibility criteria. Posters in each participating spa resort will be used for recruitment. The center is Clermont-Ferrand University Hospital associated with Royat spa center, le Mont Dore spa center and Bourbon-Lancy spa center.

Patient recruitment potential among people with knee OA in spa therapy is important. Indeed, OA represents the main disease treated by spa therapy (250,000 per year in France).

For people who meet the inclusion criteria, the research coordinator will perform the information and consent process and the physician will verify the inclusion criteria.

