### Randomisation

The population was randomized according to the alternate month design method in two arms: experimental and active comparative arm. Weingarten, highlight that’s it’s possible to avoid contamination between the 2 groups with a therapeutic window between the intervention period and control period [29]. This methodology was previously used with good level of evidence in a self-management education program and low back pain treatment in a spa therapy resort [30]. Individual randomization suggests recruitment difficulties (incomplete intervention group risk) and feasibility, as well as an increase in the number of patients lost to follow-up in the control group.

The randomisation list will be established by the methodologist in charge of the project before starting the trial. Population groups will be assigned to arms by stratified randomization by center: this randomization allows for controlling eligibility and for communicating some information relative to randomisation from the investigator and eventually other actors. A document detailing the procedures for randomisation is kept confidential. Participants will be allocated to one of two arms (Figs. 1 and 2).

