### Self-management exercise program

The main objective of the self-management exercise program will be to allow people to understand the importance of physical exercise practice and learn when, where and how to practice exercise, in order to adapt their PA practice according to their phenotype and integrate it long term in their daily life.

Each session will consist of 45 min of self-management education and 45 min of PA practice, with aerobic training program, strength training, range of motion and personal feedback. The exercise program will be tailored to each participant. The physiotherapist or adapted PA instructor will drive an experimental arm of 5 to 7 participants. The 5 sessions will take place on days (D) D4, D7, D10, D13 and D16.

For each workshop, a specific objective and operational objectives are defined, linked to criteria and indicators (Table 1).

**Table 1 Tab1:** Self-management education program

Session	Objectives
Session 1: ᅟEvaluate the representation of the patient’s PA	- Identify the representation of PA
	- Identify the barriers to and facilitators of regular PA practice
	-Acquisition of knowledge about OA
	-Know the methods of the exercise practice
Session 2: ᅟDefining the importance of exercise in knee OA	-Name the benefits of PA in the management of knee OA
	-Identify the normal and abnormal physiological signs during the PA practice
	- Learn to adapt the exercise according to its knee OA (intensity, duration)
Session 3: ᅟPatient engagement in regular PA practice	- Determine where, when and how to exercise throughout the year
	- Include an exercise program in everyday life
	- Know the anatomical bases necessary for performing the adapted exercises
Session 4: ᅟThe consequences of stopping the exercise program	-Know the importance of maintaining exercise program on a regular and long-term basis
	-Identify factors that could facilitate or limit the continuation of the exercise program
	-Learn how to build a PA session
Session 5: ᅟKnowledge restitution	- Know the means of managing knee OA
	- Know how to live healthy with knee OA
	-Set an achievable goal

*PA* physical activity, *OA* osteoarthritis

To facilitate the workshops, different teaching tools and techniques will be used: paper board, thematic discussion, participative discussion, practical leaflets (Borg scale, deconditioning circle), information booklet, exercise demonstration, feedback, and pain coping skills.

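### Arms are allocated by month within centre, but no planned analysis carries the centre-month, so the primary test does not guarantee a 5% type I error if outcomes correlate within centre-months

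*Protocol article*

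**What the plan says.** On allocation, the abstract describes a "quasi-randomized controlled trial with an alternate-month design (1-month periods"). Study design and setting repeats it: "The population will be randomised according to the alternate-month design method in 2 arms: experimental and active comparator". The Randomisation section gives the unit, "Population groups will be assigned to arms by stratified randomization by center", and argues against randomising individuals. There are three centres ("in 3 spa therapy resorts, in France"), and the trial lasts two years.

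On delivery, Self-management exercise program says: "The physiotherapist or adapted PA instructor will drive an experimental arm of 5 to 7 participants".

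On analysis, the Statistical analysis section states: "Concerning the primary outcome, the comparison between groups will be analysed using Chi-squared or" Fisher's exact tests. A logistic mixed model follows, with covariates chosen from univariate results and clinical relevance and with "centre as random-effects (to measure between and within centre variability"). The longitudinal models have patient effects nested in centre. No model names month, period or centre-month.

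**The concern.** Everyone enrolled at a given centre in a given month receives the same arm, so the unit of allocation is the centre-month. Chi-squared and Fisher tests treat each patient as separately allocated. If patients of the same centre-month resemble each other, the data hold less information about the arm contrast than the patient count suggests, and the standard error is too small.

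The follow-up models do not repair this. Both arms occur within every centre, so a centre intercept removes differences between centres but none of the between-month variation on which the arm contrast rests. A patient effect handles only repeated measures on one person.

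At stake is the error rate of the trial's single primary comparison. The article positively names the primary test and lists the random effects, and these do not match the allocation it describes. It is therefore not a detail left to an unseen analysis plan.

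**Working it through.** **Inputs from the article.** One-month periods, 3 centres, 2 years; two-sided 5%; 25% vs 5%; 65 per arm, raised to 71 (142 in total) for loss; exercise groups of 5 to 7.

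**Assumed, because the article gives neither.** ICC within centre-month: 0.02, 0.05, 0.10. Patients per centre-month: m = 2, 4, 6. The low end comes from using every month: 3 × 24 = 72 centre-months, and 142/72 = 1.97. The high end takes one exercise group per experimental month and control months of similar size.

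**The plan's own figure.** The usual pooled formula for two independent proportions is

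n = [z₁₋α/₂ √(2p̄(1−p̄)) + z₁₋β √(p₁(1−p₁) + p₂(1−p₂))]² / (p₁−p₂)², with p̄ = 0.15.

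- 80% power: (1.960 × 0.505 + 0.842 × 0.485)² / 0.04 = 48.8, so 49 per arm.
- 90% power: (1.960 × 0.505 + 1.282 × 0.485)² / 0.04 = 64.9, so 65 per arm.

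The stated 65 is not reproduced at the stated 80%; it matches 90% under independence. That is a separate matter. Here it means only that there is some slack, and that no design effect is stated.

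**Step 1: large-sample type I error of a patient-level test.** Design effect DE = 1 + (m−1) × ICC. True error = 2 × [1 − Φ(1.96/√DE)].

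| m | ICC 0.02 | ICC 0.05 | ICC 0.10 |
|---|---|---|---|
| 2 | DE 1.02, 5.2% | DE 1.05, 5.6% | DE 1.10, 6.2% |
| 4 | DE 1.06, 5.7% | DE 1.15, 6.8% | DE 1.30, 8.6% |
| 6 | DE 1.10, 6.2% | DE 1.25, 8.0% | DE 1.50, 11.0% |

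**Step 2: the two named tests, by simulation.** Beta-binomial outcomes, 65 per arm, m = 6 (11 clusters per arm), independent centre-months, no centre effect, 100,000 runs per cell. Rejection rates under the null at ICC 0 / 0.02 / 0.05 / 0.10:

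| Common rate | Chi-squared | Fisher | Fisher if an expected count is below 5, otherwise chi-squared |
|---|---|---|---|
| 5% | 4.6 / 5.8 / 7.1 / 9.8 | 1.2 / 1.7 / 2.3 / 3.7 | 1.8 / 2.5 / 3.4 / 5.1 |
| 15% | 4.7 / 5.9 / 7.6 / 10.8 | 2.8 / 3.7 / 4.9 / 7.4 | 4.7 / 5.9 / 7.6 / 10.8 |
| 25% | 5.1 / 6.3 / 8.1 / 11.2 | 3.1 / 4.0 / 5.4 / 7.8 | 5.1 / 6.3 / 8.1 / 11.2 |

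The article does not say how the choice between the two tests is made. Under the rule in the last column, Fisher applies when 65 × pooled rate is below 5, that is, below 5/65 = 7.7%. A common rate of 5% gives an expected count of 65 × 0.05 = 3.25, so Fisher is used. The design alternative, pooled at 15%, gives 65 × 0.15 = 9.75, so chi-squared is used.

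**Step 3: an analysis at the allocation unit.** A cluster-robust t-test on the difference in proportions, in the same runs at m = 6, rejected in 3.3 to 5.1% across ICC 0 to 0.10 and common rates of 5 to 25%. Its power for 25% vs 5% at 65 per arm was 90 / 87 / 83 / 76% at ICC 0 / 0.02 / 0.05 / 0.10. At m = 2 and ICC 0.10 it was 89%.

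**The case against.** The mismatch between allocation and analysis is plain on the page. What can be contested is its consequence.

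- **A reader might infer that the type I error simply exceeds 5%, in every planned analysis.** The article does not support that. It needs a positive ICC, and neither the ICC nor the cluster size is stated. Fisher, one of the two named tests, stays below 5% at a 5% common rate throughout the range examined. This stands. The protection is narrow, however: Fisher reaches 7.4 to 7.8% at common rates of 15 to 25%, m = 6 and ICC 0.10, and the logistic models do not have Fisher's conservatism.
- **Clusters may be small.** The 5 to 7 figure describes experimental exercise groups, not enrolment per centre-month, and says nothing about control months. At about 2 patients per centre-month the large-sample error is only 5.2 to 6.2%. This stands, and is why m is varied.
- **The sources of correlation may be weaker than the formula assumes.** A shared group and instructor affect only the experimental arm. With clustering in one arm at m = 6, the average design effect is (1 + DE)/2 = 1.05 / 1.125 / 1.25, and the error is about 5.6 / 6.5 / 8.0%. Season varies smoothly, and alternating months spread both arms across it. In an illustrative chi-squared simulation of a purely sinusoidal season (3 centres, 8 alternating months each, 6 patients per month), the error was 4.0 to 5.0% with one centre on the opposite order and 5.3 to 6.8% with all on the same order. Independent month-to-month shocks would inflate it more. The article does not settle which applies.
- **Ignoring the centre strata in the chi-squared test** works slightly in the conservative direction. True, but it does not offset between-month correlation by design.

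**Conclusion.** The structural point holds: allocation is by centre-month, the primary test assumes independent patients, and no planned model carries the allocation unit. The 5% level is therefore not guaranteed if outcomes correlate within centre-month.

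The size is conditional. Over the assumed ranges, the chi-squared error runs from about 5%, hardly changed, at 2 patients per centre-month and low ICC to about 11% at 6 patients and ICC 0.10. Using Fisher lowers this, and near a 5% common rate keeps it under 5%, but that is a by-product of its conservatism and not an allowance for the design. The figures assume independent centre-months with the same ICC in both arms. Clustering in one arm only would give less inflation; a month effect shared by centres on the same order would give more. A flat statement that the error is above 5% goes further than the article allows.

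**What to change.** Make the primary analysis respect the centre-month. With few events expected (65 × 0.05 is about 3 in the comparator arm), a cluster-level comparison of centre-month proportions stratified by centre is sturdier than a logistic mixed model, which may fail to converge. A cluster-robust analysis with small-sample correction and centre as a fixed effect is an alternative. A permutation test of centre-months within centre is another, but its basis should be stated: if only the starting arm of each centre is drawn and months then alternate strictly, there are just 2³ = 8 possible allocations, so the test would rest on treating months as exchangeable.

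Add a centre-month random effect to the supplementary logistic, secondary and longitudinal models. Keep chi-squared or Fisher as descriptive. State the assumed ICC and patients per centre-month, and whether the centres follow the same month order.

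The change is to the analysis text and code, and needs each patient's centre and enrolment month in the data set. The price is wider intervals and lower power. At 65 per arm and 6 per centre-month, power is about 83% at ICC 0.05, still above the stated 80%, and about 76% at ICC 0.10, below it. These figures should be given alongside the assumptions.

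### The primary test ignores the centre stratification used in allocation; a centre-stratified test with a risk difference would be a small, nearly free improvement

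*Protocol article*

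**What the plan says.** The Randomisation section describes an alternate-month design and states: "Population groups will be assigned to arms by stratified randomization by center". Participants and recruitment names three spa resorts. No quota of patients per arm within a resort is given.

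Under Statistical analysis: "Concerning the primary outcome, the comparison between groups will be analysed using Chi-squared or" Fisher's exact tests, with no stratification. The same paragraph then adds a logistic mixed model for the same outcome. It has centre as a random effect and fixed covariates selected from univariate results and clinical relevance.

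The Sample size estimation section works on the absolute scale: an "absolute difference of 20% (25% vs 5.) in the primary outcome", with "65 patients per randomized group" before loss to follow-up and 71 after it.

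**The concern.** The design uses centre as a stratum and the test that decides the trial does not. Whole months are assigned, so a resort's split between arms depends on how many eligible patients arrive in each arm's months. Stratifying the assignment of months does not hold the split at 1:1.

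If a resort with a high rate of class improvement supplies more experimental than control patients, part of the pooled difference is a resort difference, and the primary p-value includes it. The later mixed model adjusts for centre but leaves that p-value as it is. The section gives no rule for the case where the two disagree.

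There is also a mismatch of scale. The trial is sized on a difference in percentage points, while the model that adjusts for centre yields an odds ratio. The odds ratio at the planning rates is (0.25/0.75)/(0.05/0.95) = 6.33. That equals 20 points only at a 5% control rate; it is 31 points at 10% and 38 points at 15%.

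**Working it through.** **The plan's own figure.** For 25% vs 5%, two-sided 5%, the pooled-variance formula is n = [1.960·√(2·0.15·0.85) + z·√(0.25·0.75 + 0.05·0.95)]² / 0.20².
- At 80% power (z = 0.842): (0.990 + 0.408)²/0.04 = 48.8, so 49 per arm (59 with continuity correction).
- At 90% power (z = 1.282): (0.990 + 0.621)²/0.04 = 64.9, so 65 per arm.

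The stated 65 therefore matches 90% power, not the stated 80%. That is a separate matter to reconcile; here it means only that the sample has some slack.

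**Inputs for the check.** Three resorts and 142 patients (47/47/48) come from the protocol's totals, taken as evenly spread. Resort rates and arm shares are assumptions, because the protocol gives neither.

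**Bias of the pooled difference with no treatment effect.** With e and c the experimental and control counts in resort k, E and C their totals, and r the resort's rate, the expected difference is Σ(e/E − c/C)·r. It is zero if the shares are equal across resorts or if the rates are equal.

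Example with rates 5/15/30% and shares of about 40/50/60%, so e = 19, 23, 29 and c = 28, 24, 19:
- Experimental: (0.95 + 3.45 + 8.70)/71 = 13.10/71 = 18.45%.
- Control: (1.40 + 3.60 + 5.70)/71 = 10.70/71 = 15.07%.
- Spurious difference: 3.4 points.

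**Simulated rejection under no treatment effect, shares held fixed.** The first three rows use 142 patients; the last three use 130 evaluable. CMH is the Cochran-Mantel-Haenszel test stratified by centre.

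| Assumed resort rates | Experimental shares | Spurious difference | Pooled test | CMH |
|---|---|---|---|---|
| 5/15/30% | 40/50/60% | 3.4 points | about 7.3% | about 5% |
| 5/15/30% | 35/50/65% | 5.1 points | about 12% | about 5% |
| 2/5/15% | 35/50/65% | 2.6 points | about 8.7% | about 5% |
| 5/15/25% | 40/50/60% | 2.7 points | 6.7% | 4.9% |
| 5/10/15% | 40/50/60% | 1.3 points | 5.6% | 4.9% |
| 3/5/7% | 25/50/75% | 1.3 points | 5.5% | 4.2% |

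**Equal shares.** The bias is zero. At rates 5/15/30% the pooled test rejects 4.0%, and its power for a 15-point effect is 55.0% against 57.5% for CMH.

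**Shares left to chance.** If each patient is equally likely to arrive in either arm's months, a resort's share has SD √(0.25/47) = 7.3 points. Averaged over such draws, the pooled test rejects 5.0–5.1% and the mean spurious difference is 0.0 points, since imbalance favours either arm equally often. A gap of at least 20 points in share between the lowest-rate and highest-rate resorts occurs in about 5% of trials. Adding an assumed 8-point SD for uneven month volumes raises rejection to about 6% at rates 5/15/30% and 5.5% at 2/5/15%.

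**Power of CMH for the planned effect.** On 130 evaluable patients, with control rates 3/5/7% plus 20 points:
- equal shares: 92.5% (pooled 93.1%);
- shares 40/50/60%: 91.5%;
- shares 33/50/67%: 90.4%;
- shares 25/50/75%: 87.1%.

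**The case against.** The strongest reply is that the conditional error rates overstate the risk. They need arm shares that rise in step with resort rates. It is true that with random arrivals at least one of three resorts falls outside 40–60% in about 42% of trials. A reader might infer from this that 7% to 12% rejection is likely. It is not: one resort outside a band is not the ordered pattern, and averaged over arrivals the pooled test holds its level. This part of the reply stands.

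The assumed rates can also be called extreme. Rates of 5/15/30% average about 17%, against a planning control rate of 5%, and at 3/5/7% the effect is negligible. The protocol sets out to measure variation between centres; it does not predict that there will be any, and its Interventions section describes the programme as standardised across the three resorts. This stands too.

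Third, centre is not ignored: the mixed model adjusts the same outcome for it. That is correct, and a resort-driven result would meet this check. The model remains a weak safeguard. It comes after the primary test, has only three centres as a random effect and uses covariates partly picked from the data.

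Finally, a reader might infer that the 20-point difference is never estimated. The document does not support that. The two proportions being compared give the crude difference at once, and the effect measure and interval may be set out in a full plan that is not shown.

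**Conclusion.** The concern holds as a minor improvement. The primary test does not use the strata that allocation uses, and the planned adjustment for centre sits in a secondary model that leaves the primary p-value unchanged. The protocol does not show that arm shares or improvement rates differ between resorts, so it does not show that the primary result will be biased.

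The size depends on assumptions. The bias is zero if either shares or rates are equal. It is about 1 to 3 points at shares of 40/50/60% when the lowest and highest resort rates are 10 to 25 points apart, and larger only under stronger, aligned imbalance. Average type I error is about 5%, or about 6% with assumed variation in month volume. The gain is therefore protection against whatever imbalance arises in the one trial that is run, plus a little power if resort rates differ widely.

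**What to change.** In Statistical analysis, make a Cochran-Mantel-Haenszel test stratified by centre the primary test, with its exact version if the tables are sparse. Sparseness is likely: at the planning rate, 65 × 0.05 gives about 3 control improvers across three resorts.

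Beside it, report the centre-stratified Mantel-Haenszel risk difference with its 95% CI, so that the estimate is on the scale used for the sample size. As a guide to precision, 25% vs 5% with 65 per arm gives, ignoring strata, 20 ± 1.96·√(0.235/65) = 20 ± 11.8 points, or 8.2 to 31.8. The mixed model can stay as a supporting analysis.

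The cost is wording only: no new data and no extra patients. With equal shares and nearly equal resort rates, stratifying costs about half a point of power (92.5% against 93.1%). This change does not deal with the grouping of patients by month; any allowance for that would be added to it.
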